## Abstract

**Background:**

Induction of labour is a common obstetric procedure. At present, different methods are used for induction of labour in women with an unfavourable cervix. Recently, we showed that in term women with an unfavorable cervix the use of a Foley catheter in comparison with vaginal Prostaglandin E2 gel, results in a comparable vaginal delivery rate. A meta-analysis on the subject indicated lower rates of hyperstimulation, and probably as a sequel fewer cases of postpartum haemorrhage. Misoprostol (PgE1) is another type of prostaglandin frequently used for labour induction, recommended by the international federation of gynaecology and obstetrics (FIGO). Misoprostol can be administered by vaginal, rectal and oral route. There is evidence that oral administration results in less asphyxia and hyperstimulation than vaginal administration. At present, valid comparisons between oral misoprostol and Foley catheter are lacking. Therefore, we propose a randomised controlled trial comparing Foley catheter to oral misoprostol in order to assess safety and cost-effectiveness.

**Methods/Design:**

We plan a multicentre, randomised, controlled, open-label clinical trial among term pregnant women with a vital singleton in cephalic presentation, unfavorable cervix, intact membranes and an indication for induction of labour. After informed consent, women will be randomly allocated by a webbased randomisation system to transcervical Foley catheter or oral misoprostol (50 mcg every 4 hours). The primary outcome will be a composite of complications of uterine hyperstimulation, i.e. post partum haemorrhage and asphyxia. Secondary outcomes are mode of delivery, maternal and neonatal morbidity, costs and women’s preference. Serious adverse events such as severe maternal or neonatal morbitity or mortality will be monitored and reported to an independent data safety monitory board. With a sample size of 1860 women we will be able to demonstrate a 5% non-inferiority of the Foley catheter as compared to misoprostol for the composite outcome.

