### Sample size

To calculate an adequate sample size we searched the literature for comparisons between oral misoprostol and Foley catheter. There is only one study which directly compared induction of labour with oral misoprostol and Foley catheter. This study does not report on our primary outcome measures which makes it insufficient to use for our power calculation [10]. A few studies reported on a comparison of vaginal misoprostol and prostaglandin E2, but different dosages were used and from the reported outcome parameters it was not possible to calculate the composite outcome we use [6]. Therefore we used data from the PROBAAT trial, comparing prostaglandin E2 (prostin) with Foley catheter [9]. In the Probaat trial the incidence of the composite outcome of pH ≤ 7.05 and/or an Apgar < 7 at 5 minutes (at least one known) and/or haemorrhage ≥1000 cc post partum was 12.7% when a Foley catheter was used and 16.4% when Prostaglandin E2 gel was used. We expect the incidence of the composite outcome to be lower when using oral misoprostol than when using prostaglandin E2 but slightly higher than when a Foley catheter is used [5]. We expect that about 25% of umbilical cord pH’s will be missing, while the 5 minute Apgar will be complete in nearly all cases. So, if the umbilical artery pH data will be missing, neonatal outcome will be classified as abnormal if the 5 minute Apgar will be <7 and as normal if the Apgar was ≥ 7. With a power of 80% (1-β) and a one-sided 0.05 risk of type I error (α), we need 1860 participants (930 per group) to demonstrate non-inferiority, i.e. that the absolute difference in the composite outcome will be less than 5% in the misoprostol group compared to the Foley catheter group, when assuming that the composite outcome was 12.7% in the Foley catheter group and 13.7% in the misoprostol group and an 5% exclusion rate from the per protocol analysis. This sample size will also give us more than 80% power to demonstrate non-inferiority, i.e. less than 5% increase in the proportion of caesarean sections when using misoprostol compared to Foley catheter, assuming 23% caesarean sections in both groups [9]. We used NQuery Advisor 7.0, with the two group test of equivalence in proportion (NQueryAdvisor; Machin 1987) to calculate the sample size.

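### The abstract tests Foley against misoprostol, but the sample size tests misoprostol against Foley, so the primary non-inferiority hypothesis points both ways

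*Protocol article*

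**What the plan says.** **Abstract, Methods/Design.** With 1860 women, "we will be able to demonstrate a 5% non-inferiority of the Foley catheter as compared to misoprostol for the composite outcome". Foley is the arm to be shown non-inferior; misoprostol is the reference.

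**Sample size.** The article states that "we need 1860 participants (930 per group) to demonstrate non-inferiority", and defines this as showing "that the absolute difference in the composite outcome will be less than 5% in the misoprostol group compared to the Foley catheter group", "assuming that the composite outcome was 12.7% in the Foley catheter group and 13.7% in the misoprostol group", with "an 5% exclusion rate from the per protocol analysis". Power is 80% and alpha is 0.05 one-sided. Here misoprostol is the tested arm and Foley the reference. The same section uses the same direction for caesarean section: "less than 5% increase in the proportion of caesarean sections when using misoprostol compared to Foley catheter". The abstract makes no statement about caesarean section.

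**Analysis.** The trial is described as a non-inferiority trial, with no tested arm, reference arm or sign. Relative risks with 95% intervals are planned, whereas the margin is an absolute difference.

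**Aims.** Foley is assessed in comparison with misoprostol. This leans towards the abstract but states no hypothesis.

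**The concern.** A non-inferiority hypothesis is one-sided. It has no meaning until the plan says which arm may be worse, and by how much. This article gives two opposite answers for the same primary outcome, margin and number of women.

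The two hypotheses are not equally hard to satisfy. Foley is expected to do slightly better, so showing that Foley is not much worse is easy, and showing the same for misoprostol is much harder. Under the abstract the trial would succeed even if misoprostol were more than 5 points worse; under the Sample size section it would fail. With both versions in the text of an open-label trial, the direction could be settled after the results are known, and a reader could not tell which claim had been planned.

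**Working it through.** **Inputs** (Sample size section): composite outcome 12.7% with Foley and 13.7% with misoprostol (an adverse outcome, so higher is worse); margin 5 points absolute; one-sided alpha 0.05; power 80%; 5% excluded from the per-protocol analysis; 930 per group. Allocation is 1:1 (Procedures section).

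**Formula** (unpooled variance): n per group = (z₀.₉₅ + z₀.₈₀)² × [p_F(1−p_F) + p_M(1−p_M)] / d², where d is the margin minus the assumed true excess in the tested arm.

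- (1.6449 + 0.8416)² = 6.183
- 0.127 × 0.873 + 0.137 × 0.863 = 0.1109 + 0.1182 = 0.2291
- Evaluable per group after exclusion: 930 × 0.95 = 883.5
- Standard error of the difference: √(0.2291 / 883.5) = 0.0161
- Power = Φ(d / 0.0161 − 1.6449)

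| | Misoprostol tested (Sample size) | Foley tested (abstract) |
|---|---|---|
| d | 0.05 − 0.01 = 0.04 | 0.05 + 0.01 = 0.06 |
| n per group | 885.3 | 393.5 |
| n / 0.95 | 931.9 | 414.2 |
| Power, 883.5 per group | 79.9% | 98.1% |
| Power, 930 per group | 81.7% | 98.5% |

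The plan's 930 is reproduced, to within rounding, with misoprostol tested. With Foley tested, the requirement is under half of it. At one-sided 0.025 the totals would be 2368 and 1054, and neither is 1860.

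**Caesarean section.** With 23% in both groups and a 5-point margin, power is 80.3% at 883 per group. The assumed rates are equal, so this figure is the same in either direction and does not help to decide between them.

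**How the verdict depends on the direction.** Suppose 12.7% with Foley and 15.7% with misoprostol are observed, 883.5 per group.

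- Standard error: √[(0.127 × 0.873 + 0.157 × 0.843) / 883.5] = 0.0166; 1.6449 × 0.0166 = 0.0273.
- One-sided 95% upper limit of misoprostol minus Foley: 3.0 + 2.7 = 5.7 points, above 5. Misoprostol is not shown non-inferior.
- One-sided 95% upper limit of Foley minus misoprostol: −3.0 + 2.7 = −0.3 points, below 5. Foley is non-inferior with room to spare.

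A gap of this size is plausible: the Sample size section reports 16.4% against 12.7% (3.7 points) for prostaglandin E2 gel and Foley in the earlier trial.

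**How often the verdicts would differ.** Under the plan's own assumptions, misoprostol fails in 100 − 79.9 = 20.1% of trials and Foley in 100 − 98.1 = 1.9%. At this size both cannot fail at once: that would need 1.6449 standard errors to exceed 5 points, and they come to 1.6449 × 1.61 = 2.65. The two hypotheses would therefore give different verdicts in about 20.1 + 1.9 = 22% of trials.

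**The case against.** The case against rests on four points.

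1. *The abstract's statement is not numerically false.* It gives no power figure, and 1860 women do suffice to show Foley non-inferior, with about 98% power. This stands. The trial is not underpowered in either direction; the defect is in the definition of success.

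2. *One summary sentence conflicts with a methods section that is consistent with itself.* The Sample size section gives the same direction twice, and the arithmetic supports it. This makes misoprostol the likelier intended tested arm. But no formal hypothesis or decision rule elsewhere overrides the abstract, and the Aims lean the other way.

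3. *The software procedure named in the Sample size section is a test of equivalence, which would bound the difference in both directions.* Read as two one-sided tests at 0.05, power is about 80% at 930 per group, so on that reading 930 can be reached without any exclusion allowance. With the stated 5% exclusion it is 79.9 + 98.1 − 100 = 78%, short of target. The text also speaks of a one-sided error, non-inferiority and an increase. The equivalence reading is therefore less consistent with the section, but the named procedure leaves a further ambiguity to clear up.

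4. *Choosing the direction afterwards is speculation.* No such intention is alleged. The point is that the document would not prevent it.

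The conflict is confined to the composite outcome, since the abstract is silent on caesarean section.

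**Conclusion.** The concern holds. The abstract and the Sample size section state opposite non-inferiority hypotheses for the primary outcome, and no other part of the article resolves them. The stated 930 per group, with its 5% exclusion, follows from misoprostol as the tested arm (932 by calculation). The abstract's direction would need about 414. Power with 1860 women is about 80% or about 98%, depending on the direction, and the two verdicts would differ in about 22% of trials under the planning assumptions.

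These figures rest on the article's rates, margin, alpha and exclusion rate, and on the normal approximation with unpooled variance. The number of women does not need to change. The matter must still be fixed, because what counts as success on the primary outcome is undetermined until it is.

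**What to change.** State one hypothesis, with the tested arm, reference arm, sign of the difference and confidence limit, and use it in the abstract, Sample size and Analysis sections.

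- **If misoprostol is tested**, which matches the calculation: H0: p(misoprostol) − p(Foley) ≥ 5 points. Conclude non-inferiority if the upper one-sided 95% limit of that difference is below 5 points. Reverse the abstract sentence so that it claims non-inferiority of misoprostol as compared with the Foley catheter. The 1860 stands.
- **If Foley is tested**: keep the abstract, reverse both the composite and the caesarean statements in the Sample size section, and restate the power for the composite as about 98%.

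In either case, put the decision rule in the Analysis section on the risk-difference scale, and describe the sample-size procedure as one-sided non-inferiority if that is what was used.

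The cost is a wording amendment with no extra patients. The article does not give recruitment status, and interim analyses are planned at 300 and 600 women. The change should be made and dated before anyone deciding on it has seen comparative data.

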**Discussion:**

Worldwide, various methods are being used for labour induction. Results of the proposed trial will contribute to the answer which method of induction of labour is most safe, cost-effective, and patient friendly and will help to construct evidence based guidelines.

**Trial registration:**

The Netherlands Trial Register NTR3466

## Background

Induction of labour is a commonly practiced obstetric intervention designed to artificially initiate the process of effacement of the cervix, dilatation (cervical ripening), uterine contractions (often after augmentation with oxytocin) and eventually delivery of the baby. Common indications for induction of labour are post-term pregnancy, hypertensive disorders, diabetes in pregnancy, cholestasis, decreased physical activity of the fetus and prelabour rupture of membranes. Induction of labour with an unfavorable cervix is associated with prolonged labour compared to spontaneous onset of labour or induction of labour with a favorable cervix. Also an increase in instrumental deliveries and a higher rate of caesarean sections are seen [1-3]. To increase the success of labour induction it is essential to achieve cervical ripening in women with an unfavorable cervix. Misoprostol has been widely studied as an agent for induction of labour. There are currently two Cochrane reviews focusing on the use of both oral and vaginal misoprostol [4,5]. These systematic reviews conclude that misoprostol is an effective and safe induction agent. Oral misoprostol is preferred to vaginal administration for as it shows lower rates of uterine hyperstimulation and adverse neonatal outcome [4,5]. Although not licensed for induction of labour, misoprostol is recommended by several guidelines. The British Royal College of Obstetricians and Gynaecologists (RCOG), as well as the World Health Organization (WHO), recommend the use of misoprostol tablets, based on cost-effectiveness. In the Dutch Society of Gynaecology and Obstetrics (NVOG) guideline for induction of labor, misoprostol is included and reported to be effective and safe [6-8]. Another method for induction of labour is the transcervical Foley catheter. We recently showed (PROBAAT trial) that induction of labour with a Foley catheter is as effective as induction with intravaginal prostaglandin E2 gel, with fewer maternal and neonatal side-effects [9]. The caesarean section rate was comparable and in the meta-analysis of three trials on the subject, the Foley catheter revealed a lower rate of hyperstimulation, resulting in fewer cases of asphyxia and less post partum haemorrhage. Consequently, the transcervical Foley catheter was recommended for induction of labour in women with an unfavorable cervix at term [9]. The Foley catheter is reported to have similar success rates as induction of labour with misoprostol (vaginal and oral), and is associated with less uterine hyperstimulation with and without fetal heart rate (FHR) changes and a comparable caesarean section rate [10-14]. As prostaglandins in general have been shown to cause an increased incidence of hyperstimulation, we expect a decreased blood flow of the placenta and consequently an increased the risk of asphyxia. In addition, hyperstimulation might lead to uterine muscle fatigue and thereby increase the risk for post partum haemorrhage. However, randomised controlled trials currently available are underpowered to investigate these estimators. In view of the scarce evidence on the subject, we propose a adequately-powered randomised controlled trial comparing induction of labour with a Foley catheter to induction of labour with oral misoprostol in women with an unfavorable cervix at term. In this trial the safety, cost-effectiveness and patient preference will be evaluated.

## Methods/Design

### Aims

The aim of this study is to assess the safety and cost-effectiveness of induction of labour with a transcervical Foley catheter as compared to induction with oral misoprostol in term pregnant women with an unfavourable cervix.

### Participants/eligibility criteria

Term pregnant women will be informed about the trial at the moment the decision is made to induce labour. Eligible are women ≥ 18 years with a gestational age ≥37 weeks with a vital singleton in cephalic presentation, intact membranes and an unfavourable cervix (Bishop score <6). Exclusion criteria are hypersensitivity for any of the products used, a history of caesarean section, placenta praevia, or lethal congenital anomalies.

### Procedures, recruitment, randomisation, collection of baseline data

This trial will be a multicentre, open-label, randomised controlled trial. The study will be performed within the Dutch Consortium for Studies in Women’s Health and Reproductivity (http://www.studies-obsgyn.nl). Participating hospitals can be district, teaching or academic hospitals. Before entry into the study, women will be informed about the aims, methods, reasonably anticipated benefits and potential hazards of the study. This will generally be at least 1 day before actual admission for induction. They will be informed that their participation is voluntary and that they may withdraw consent for participation at any time during the study. Choosing not to participate will not affect care. In each centre an independent physician will be available for more detailed information for both patients and colleagues if desired. After counselling, written informed consent will be obtained. The consent form must be signed before performing of any study-related activity. Randomisation will be performed web-based using ALEA. After entering patient initials, confirming inclusion criteria and absence of exclusion criteria, randomisation will be performed realtime based on an algorithm. We will use fixed block sizes of 2 and 4 and stratify for centre and parity. As there is no prespecified randomisation list, it will be hardly possible for anyone to know the next allocation. Randomisation will take place after evaluation of the fetal condition by CTG, just before start of induction. Eligible women will be allocated in a 1:1 ratio to induction with a Foley catheter or oral misoprostol. There will be no blinding of patients and caregivers, as this is not feasible with these two treatment methods. Baseline demographic, obstetric and medical histories, and details of delivery and health care received till the time of discharge will be recorded for all women. Data will be entered into an electronic case-record form (Oracle Clinicle version 4.5.3) accessible through our study website with a personal login http://www.studies-obsgyn.nl/probaat2. All changes made in this electronic case-record form will be captured in an audit trial. In Oracle Clinicle checks will be programmed to identify errors. All electronic case-record forms will be checked for consistency and to correct errors.

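### Blocks of 2 and 4 within centre-by-parity strata make the next allocation guessable in this open-label trial, and the absence of a stored list does not prevent that

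*Protocol article*

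**What the plan says.** All the relevant statements are in the protocol article, section on procedures, recruitment, randomisation and baseline data.

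- Scheme: "We will use fixed block sizes of 2 and 4 and stratify for centre and parity". The ratio is 1:1.
- Process: "After entering patient initials, confirming inclusion criteria and absence of exclusion criteria, randomisation will be performed realtime based on an algorithm".
- Timing: "Randomisation will take place after evaluation of the fetal condition by CTG, just before start of induction".
- Blinding: "There will be no blinding of patients and caregivers, as this is not feasible with these two treatment methods".
- Concealment: "As there is no prespecified randomisation list, it will be hardly possible for anyone to know the next allocation".

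The same section says that women are generally informed at least a day before admission and sign consent before any study activity.

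**The concern.** The concealment sentence gives one reason, the lack of a stored list, and that reason does not bear on the problem. In permuted blocks the next allocation is constrained by those already made in the block. It makes no difference whether the sequence was written down in advance or produced on demand. Each stratum lies within one centre, treatment is open, and the article prints the block sizes. Staff who remember which arm is behind among recent women of the same parity therefore have useful information about the next allocation.

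What is at stake is selective entry. Randomisation follows the CTG, so prognostic information is at hand when a guess could be used, and the Bishop score below 6 is a judged entry criterion. If women at higher or lower risk are entered preferentially when a particular arm is expected, the arms differ at baseline. Intention-to-treat analysis, per-protocol analysis and adjustment for the stratification factors do not correct that.

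**Working it through.** The plan gives no figure for predictability, so there is none to reproduce. The sample size of 1860 does not depend on the block scheme.

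**Inputs.** From the article: block sizes 2 and 4, 1:1 ratio, strata by centre and parity, open label. Assumed, because not stated: the two sizes are equally frequent. An average cycle is then one block of each size, 6 allocations.

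**Block of 2.** The first allocation is a coin toss and the second is fixed. Certain: 1 of 2 (50%). Correct guesses: 0.5 + 1 = 1.5 of 2 (75%).

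**Block of 4**, guessing the arm that is behind:
- Position 1: arms equal, 0.5 correct.
- Position 2: always unequal, 2/3 correct.
- Position 3: with probability 1/3 the first two were alike and the third is fixed; otherwise the arms are equal. Correct: 1/3 + (2/3)(0.5) = 2/3.
- Position 4: always unequal and fixed, 1 correct.

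Correct: 0.5 + 2/3 + 2/3 + 1 = 2.833 of 4 (70.8%). Certain when the size is known: 1/3 + 1 = 1.333 of 4 (33.3%).

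**Equal mix of 2 and 4.**
- Arms unequal before an allocation: (1 + 1 + 1/3 + 1)/6 = 3.333/6 = 55.6%.
- Correct when unequal: (1 + 2/3 + 1/3 + 1)/3.333 = 3/3.333 = 90%.
- Correct overall: (1.5 + 2.833)/6 = 72.2%.
- Certain, sizes known: (1 + 1.333)/6 = 38.9%.
- Certain, sizes mixed at random and unknown: only an imbalance of two reveals a block of 4, and it fixes the next two allocations. This gives 2 × (1/3)/6 = 11.1%.

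The 90% and 72.2% need no knowledge of the current block size, only the running balance in the stratum.

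**Sensitivity.** In simulation with strata of 10 to 60 women and sizes unknown, about 10–11% of allocations were certain and 71–72% were guessed correctly. With the share of blocks of 2 varied from 1/3 to 2/3, the ranges were 8–13% and 71–73%. A Bayesian guesser did no better than the simple rule.

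**Blocks of 6, 8 and 10, equally mixed (24 allocations per cycle).** In a block of 2m the expected number of allocations made with the arms equal is E = 4^m/C(2m,m) − 1, and correct guesses when unequal total m.
- E = 2.200, 2.657 and 3.063; sum 7.921.
- Unequal: (24 − 7.921)/24 = 67.0%.
- Correct when unequal: (3 + 4 + 5)/16.079 = 74.6%.
- Correct overall: (12 + 0.5 × 7.921)/24 = 66.5%.
- Certain, sizes known, using 2m/(m + 1) per block: (1.5 + 1.6 + 1.667)/24 = 19.9%.

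| Scheme | Unequal | Right when unequal | Right overall | Certain, sizes known |
|---|---|---|---|---|
| 2 and 4 | 55.6% | 90% | 72.2% | 38.9% |
| 6, 8 and 10 | 67.0% | 74.6% | 66.5% | 19.9% |

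**Illustration of consequence (assumption, not in the documents).** Suppose every entry were steered, so that a woman's risk is d points higher or lower according to the guessed arm. The spurious arm difference is 2 × (2 × 0.722 − 1) × d = 0.89d. For d = 1 to 3 points that is 0.9 to 2.7 points, against the 5-point margin in the sample size section. This is an upper bound under full exploitation, not an estimate.

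**The case against.** The strongest defence has four parts.

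1. **Predictable is not known.** A reader might infer that half, or a third, of allocations are known with certainty. Those figures need staff to know the block size in use and where the block began. The article names two sizes without saying whether they are mixed at random, alternated or assigned by stratum, a detail that a full protocol may settle. Under random mixing with sizes unknown, about 11% are certain and the rest of the advantage is better-than-chance guessing. This stands and limits the size of the point.

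2. **Safeguards exist.** Information is generally given a day or more ahead, consent comes first, eligibility is confirmed in the web system, and randomisation comes last. A guess made at the time of the offer may be out of date by entry. This stands in part: staff could still delay or withhold entry of a consented woman at the moment when the guess is current.

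3. **Exploitation is not shown.** Staff would have to follow the running balance by parity within their centre, and nothing in the article describes this or a display of past allocations. This stands.

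4. **Larger blocks help only moderately.** Overall correct guesses fall by about 6 points (72.2% to 66.5%), and the arms are unequal more often. This stands, although the near-certain guesses, which are the useful ones, become markedly fewer.

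None of this rescues the stated reason. Forced balance acts with or without a list.

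**Conclusion.** The concealment sentence is wrong in its reasoning, and the scheme it defends is more guessable than an open-label trial needs. With an equal mix of 2 and 4, the lagging-arm rule is right 90% of the time in the 56% of allocations with unequal arms, and 72% overall. Certainty runs from about 11% (random mix, sizes unknown) to 39% (sizes known), reaching 50% only in strata made up wholly of blocks of 2. These figures assume that staff know the running balance in their stratum.

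Two stronger readings are not supported. One is that the trial is biased: the documents show an opening for selective entry, not its use, so the bias is a risk of unknown size. The other is that no analysis could help. Baseline demographic, obstetric and medical history is recorded for all women, so measured imbalance can be examined and adjusted for; only unmeasured selection would remain. That blood loss is estimated without blinding is a separate matter of outcome assessment. It does not cause baseline imbalance, and changing the blocks would not affect it.

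**What to change.** - Use larger, randomly varied block sizes, for example 6, 8 and 10, within the same centre-by-parity strata.
- Withhold the sizes from sites and from public text.
- Delete or correct the sentence that rests unpredictability on the lack of a list. If something is to replace it, say that sizes vary at random and are not disclosed to centres.
- If recruitment has started, report the block scheme actually used, including how sizes were combined, and compare baseline characteristics by predicted allocation (the arm that was behind in the stratum before each woman's entry).

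**Cost.** This is a setting in the web randomisation system, and the sample size is unchanged. The largest possible imbalance within a stratum rises from 2 to 5, and small strata may end with incomplete blocks. The number of centres is not stated, so stratum size should be checked before the upper block size is fixed.
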